#### Evaluation of school lunch and compensation effects as assessed by parents

Descriptive statistics will be used to examine the compensation questionnaire among parents. Chi-square tests of independence will be computed for ordinal answers on compensation questions in the questionnaire to identify statistically significantly differences among parent groups (comparison versus intervention schools).

Each session of the group discussions with parents will be audiotaped. During the sessions, notes will be taken by at least two researchers. After the discussion, these two researchers will discuss and summarize their main findings.

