Overall, children’s diet is an important contributor to their development and growth and overall health in later life. Eating habits that are adopted in childhood often persevere into adulthood [15] and therefore it is important to teach and stimulate healthy eating practices as early as possible. Therefore, the aim of this study is to encourage healthy eating during lunch of children in the primary school setting by offering a healthy school lunch, based on the Dutch guidelines for a healthy diet. In this study, two research questions will be addressed. The first research question is: What, how much and how healthy do children consume from a self-served school lunch and how do they evaluate the lunch? The second research question is: Do children compensate healthier school meals by eating less healthy outside school hours?

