#### Evaluation of school lunch and compensation effects as assessed by parents

A questionnaire will be administrated among parents of the three intervention schools and three comparison schools to assess potential compensation effects. Potential compensation effects due to the school lunch are probably small. To be able to measure these small effects on total dietary intake per day, several full measuring days would be required per child which makes it unlikely that the majority of children and parents would participate in extensive dietary intake measures (especially for control schools). If there are any compensation effects after school, then parents are probably the first to notice. That is why we have opted for a direct method of explicitly asking parents if they see differences in their child’s dietary intake. As parents of intervention schools are aware of the objective of the healthy school lunch, they could be more inclined to give socially desirable answers. Therefore, it is important to compare their answers with parents from schools without intervention.

To better understand how parents evaluate the school lunch and perceive their children’s eating and drinking during school lunch, one group discussion with parents at each of the intervention schools will be conducted.

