##### Brief questionnaire on potential compensation effects

This questionnaire focuses on parents’ perception of changes in consumption outside school hours during the final month of the school lunch period. To increase the response rate, the questionnaire was kept very brief and were told to keep their oldest child at primary school in mind. Questionnaires will be distributed both via school e-mail and paper.

First, parents will be told the following: ‘We are curious to know whether your child started to eat differently during the past six months (since autumn holiday till now). Could you indicate whether your child eats less, about the same or more of the following products at home compared to six months ago? If you do not know, then you fill in ‘I do not know’. The following products were then mentioned: ‘snack vegetables, such as tomatoes, cucumber, radish, carrot’, ‘vegetables during the evening meal, warm or cold such as lettuce and salad’, ‘sweet snacks such as cookies, chocolate or candy’, ‘savory snacks, such as crisps, cheese or warm snacks’, ‘juice, lemonade or soft drinks with sugar (no diet)’ and ‘water, milk and sour milk’. Answer possibilities will be: ‘eating less’, ‘eating about the same’, ‘eating more’ and ‘I do not know’.

Next, parents will be asked ‘Does your child has now more or less appetite (desire for food) immediately after school compared to six months ago?‘ with answer options ‘now less appetite’, ‘about the same appetite’, ‘now more appetite’, and ‘I do not know’. The same question was asked regarding appetite during the evening meal.

Finally, parents were asked to indicate the group of their oldest child at the school and were given the opportunity to comment to the question: ‘Are there other things that you noticed with regard to the eating behavior of your child in the past six months? For example, are there foods or drinks your child asked for or talked about? Do you have any more suggestions or questions for the researchers?’

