## Discussion

This study will be conducted to assess the impact of providing a healthy school lunch on dietary intake of children during lunch of primary schools in the Netherlands. The primary outcome measures of this study focus on how much and healthy children consume from the school lunch. A secondary objective is to assess the degree of compensation of eating less vegetables, or more unhealthy snacks and drinks outside school hours. Lunch at school is typically not provided in the Netherlands, but has traditionally been consumed at home or brought from home by children themselves and eaten at school. A healthy lunch provided by school therefore presents many changes for children, parents and the school. We hypothesize that the school lunch will lead to an increase in vegetable consumption.

A strength of this study design is that it focuses on the development of a school lunch that is acceptable for children, parents and schools in various ways. The lunch was tailored to their needs to improve the likelihood of acceptance and the evaluation of the school lunch will be assessed among both children, parents and school teachers. In this way, it is most likely that healthier school lunch eating behavior is encouraged. Moreover, we measure potential compensation effects of the school lunch as assessed by parents, as unwanted compensation effects are a major concern when improving school food environments [25].

Some limitations should be noted about the design. Only three intervention and three comparison schools participated with children of grades 5 till 8. Moreover, there may be other explanations of why consumption of key food groups of interest may have changed during the school day. The limited intervention period of six months may be insufficient to obtain sustainable behavior changes and acceptance of the lunch. In addition, a voluntary financial contribution will be asked from parents, but this may not be feasible for certain income groups. These issues are important to consider in future research and implementation practices.

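### The parent compensation items are ordered and the question is directional, but the planned chi-square test ignores both order and direction

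*Protocol article*

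**What the plan says.** Research question 2 (Background) is: "Do children compensate healthier school meals by eating less healthy outside school hours". The Discussion calls this a secondary objective and gives it a direction: "the degree of compensation of eating less vegetables, or more unhealthy snacks and drinks outside school hours".

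The brief parent questionnaire asks: "Could you indicate whether your child eats less, about the same or more of the following products at home compared to six months ago". It lists six product groups. A question on appetite right after school follows, and then: "The same question was asked regarding appetite during the evening meal". That makes eight items. Each has three ordered answers plus 'I do not know', introduced in the product question with "If you do not know, then you fill in".

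Under Data analysis, descriptive statistics are planned first. Then: "Chi-square tests of independence will be computed for ordinal answers on compensation questions in the questionnaire", to compare parents at intervention and comparison schools. On effect size, the Outcome measures section says only: "Potential compensation effects due to the school lunch are probably small". The article gives no expected number of parents and no expected answer split.

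**The concern.** The analysis sentence calls the answers ordinal and then names a test that discards their order. The question is whether intervention parents report a shift in one particular direction. The test asks only whether the two answer distributions differ in any way.

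Three things are at stake for research question 2:

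- A significant result need not mean net compensation.
- For the most natural alternative, a shift along the scale, the test is less sensitive, and the effects are expected to be small.
- A p-value alone does not say how much compensation could have gone unseen.

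This is a stated choice of method, not a detail left to a fuller document.

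**Working it through.** The article has no figure of its own for the parent comparison. Its only sample-size result, 134 children, belongs to the vegetable outcome and is not affected here.

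**Inputs.** From the article: three ordered answers plus don't-know, eight items, 3 versus 3 schools. Assumed: 150 parents per group unless stated, the answer splits below (% less/same/more), and a two-sided 5% level, which the article states only for the vegetable calculation.

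**1. Power for a shift along the scale.** A 1-df test at 5% has 80% power at noncentrality 7.85. With the same noncentrality:

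- 2 df (three categories): power 70.9%
- 3 df (don't-know kept as a fourth column): power 64.5%

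Restoring 80% needs noncentrality 9.63 or 10.90, so 9.63/7.85 = 1.23 or 10.90/7.85 = 1.39 times as many parents.

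**2. Rejection rates by pattern** (simulated, 150 per group, control 10/80/10, don't-knows excluded). The last column is a simple test of the share answering 'more'.

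| Intervention | Chi-square, 2 df | Linear trend, 1 df | Share 'more' |
|---|---|---|---|
| 6/78/16 (shift along scale) | 38% | 47–48% | 34% |
| 16/68/16 (spread, no net shift) | 56% | 5% | 34% |
| 20/60/20 (wider spread) | 94% | 5% | 69% |
| 10/70/20 (same to more only) | 59% | 42% | 69% |

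The chi-square rejects often under a pure spread, where the mean answer does not move. It loses to the trend test for a shift and beats it when parents move only from same to more. In that last pattern the share comparison does best.

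**3. Don't-knows, if kept as a column.** With identical answers among parents who do answer (10/80/10), and don't-know rates of 5% versus 15%, the four-category chi-square rejects 29%, 49% and 69% of the time at 60, 100 and 150 per group. With don't-knows dropped, rejection stays at about 5%.

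**4. What a non-significant result leaves open.** With an assumed 15% answering 'more' in both groups, the 95% CI half-width for the difference is 1.96 × √(2 × 0.15 × 0.85 / n):

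- n = 60: 12.8 points
- n = 100: 9.9 points
- n = 150: 8.1 points
- n = 200: 7.0 points

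These ignore clustering. With an assumed ICC of 0.02 and 45 parents per school, the design effect is 1 + 44 × 0.02 = 1.88. Intervals widen by √1.88 = 1.37, and a nominal 5% test rejects about 15% of the time.

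**5. Eight items.** If they were independent and each tested at 5%, the chance of at least one false positive is 1 − 0.95^8 = 33.7%. Items answered by one parent about one child are correlated, so the true figure is lower.

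**The case against.** A chi-square on a three-level answer is a valid test, and the claim that it wastes power does not hold for every pattern. If a subset of children compensates and the rest do not change, parents move only from same to more, and the chi-square beats the trend test (59% versus 42%). That stands, and it is why an ordinal p-value should not be the only replacement.

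The plan is also not limited to significance tests. Descriptive statistics are promised, and the direction of a difference could be read from them. That stands too, but a reader would then be pairing an undirected p-value with a direction judged by eye.

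Three stronger readings are tempting and not supported:

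- *That don't-knows will drive the test.* The chi-square is to be applied to ordinal answers, and don't-know is not on the ordered scale. The natural reading may be that it is left out. The article does not settle this, and a fuller plan might.
- *That the authors will conclude there is no compensation from a non-significant result.* The article announces no such conclusion and no decision rule. The point limits interpretation; it is not an error in the text.
- *That eight items carry a 34% false-positive risk.* That figure is an upper-end value under independence, and the article states no alpha for these tests.

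**Conclusion.** The concern holds in this form: an undirected test is named for ordered answers to a directional question. Where a 1-df ordinal test has 80% power for a shift along the scale, the planned test has about 71%. It can reject in more than half of studies under a symmetric spread with no net shift, and its p-value gives no bound on undetected compensation. With 100 to 200 parents per group, the uncertainty on the share answering 'more' is roughly 7 to 10 points either way before clustering.

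The 71% follows from the degrees of freedom alone. The other figures rest on assumed splits, don't-know rates and parent numbers. The power loss depends on the pattern, and the don't-know problem arises only if that answer is kept as a column. Because this is a secondary objective and the primary vegetable outcome is untouched, the change is worth making but is not critical.

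**What to change.** For each of the eight items:

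1. Report 'I do not know' by group as its own line and leave it out of the test.
2. Replace the chi-square with an ordinal comparison: linear trend, Wilcoxon or proportional odds.
3. Give as the main estimate the between-group difference in the share answering in the compensating direction, with a 95% CI that allows for parents being clustered in schools. Say plainly that 3 versus 3 schools limits how well this can be done. Show the share answering in the opposite direction beside it, so that a spread can be told from a shift.
4. State the compensating direction for each item beforehand. The Discussion gives it for vegetables and for unhealthy snacks and drinks, but not for the water and milk item or the two appetite items.

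Add that a non-significant result is not evidence of no compensation, and that the eight items are interpreted as a set, with a multiplicity adjustment if claims are made for single items.

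**Cost.** Slightly more analysis work and no new data. Data collection is complete and analysis was under way at submission, so the change should be dated and reported as such. The ordinal test is less sensitive when parents move only from same to one extreme; the directional share in step 3 covers that case.

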## Methods

### Study design

In the Healthy School Lunch project children in grades 5–8 (aged 8–12 years) of three primary schools in the Netherlands will receive a healthy school lunch for a 6-month period (November 2018 to April 2019). The development of this healthy school lunch is guided by a study among parents and children about desired school lunch concepts [16, 17]. Important to note is that in the Netherlands, it is very common for children to take all their foods and drinks from home (morning snack and lunch). There is no opportunity to buy food or drinks at primary school and there is no national subsidized school lunch program which offers school meals. Most primary schools in the Netherlands report to have a written food policy (e.g. on what is allowed to bring) although there is no legal obligation to do so [18].

To answer research question 1, we will collect lunch consumption data by means of pictures. All intervention group children will have to complete an initial baseline measurement in the situation where they still bring their own packed lunch. They will also have to complete a second and third follow-up questionnaire at month 3 half-way and month 6 at the end of the period in which a healthy school lunch will be provided.

To answer the second research question, a quasi-experimental, intervention-comparison group design (3 intervention schools and 3 comparison schools) will be carried out. There will be no randomization of the intervention and comparison schools, as the schools had to fully agree and decide on their participation beforehand, which required consent from their stakeholders (teachers, parents, support staff). Potential compensation effects will be measured with a single brief questionnaire among parents both at the three intervention schools and at the three comparison schools at month 6 of the lunch period. The school lunch will also be evaluated by parents (discussion groups) and teachers and support staff (brief questionnaire).

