Schools were situated in the capital of the Netherlands Amsterdam and in two small cities, i.e. Lunteren and Vlaardingen (10.000–100.000 inhabitants). Two of the three schools are situated in a district characterized by residents with a lower SEP (Amsterdam and Vlaardingen) and one in a semi-rural town with children of parents with a relatively high SEP (Lunteren). Comparison schools were recruited to match these SEP levels. All children of grades 5 till 8 were invited to participate in the study. Children of grades 1 to 4 were not invited. This was done given budget constraints and we expected that older children would be better able to reflect on their experiences in the questionnaire. Children and parents who decided to join the lunch after the start will also be enrolled. Consequently, data at baseline can be missing for these children. Letters will be sent to parents to explain the study and school lunch. At each school, information meetings will be set up to inform all parents and children. All parents of children that participate will be send a letter after about three months with an invitation to give feedback about the school lunch. This evaluation is not part of the measures, but will be used to adapt and improve the intervention if necessary.

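### The compensation items are tested with chi-square tests that pool parents by condition, although condition was set by school (3 versus 3), so the false-positive rate exceeds 5% whenever answers correlate within school

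*Protocol article*

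**What the plan says.** Under *Data analysis*, in the part on compensation effects as assessed by parents, the protocol article first plans descriptive statistics and then names the test: "Chi-square tests of independence will be computed for ordinal answers on compensation questions in the questionnaire". The purpose is "to identify statistically significantly differences among parent groups (comparison versus intervention schools").

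The *Study design* section gives the structure of the comparison: "a quasi-experimental, intervention-comparison group design (3 intervention schools and 3 comparison schools) will be carried out". It adds: "There will be no randomization of the intervention and comparison schools". On timing it says: "Potential compensation effects will be measured with a single brief questionnaire among parents both at the three intervention schools", and likewise at the comparison schools, at month 6.

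On the make-up of the groups, *Recruitment* says of the intervention schools: "Two of the three schools are situated in a district characterized by residents with a lower SEP". The third has a relatively high SEP. It continues: "Comparison schools were recruited to match these SEP levels".

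The parent questionnaire has eight closed items, six on foods and drinks and two on appetite. For the food items: "Answer possibilities will be: ‘eating less’, ‘eating about the same’, ‘eating more’ and ‘I do not know". The appetite items have the same four-option form.

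Clustering is mentioned once, under *Recruitment*, as one reason for enrolling more children than the calculated number. No ICC or inflation factor is given, and the parent analysis does not mention clustering.

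**The concern.** A chi-square test of independence takes its error from variation between individual parents. Here condition varies only between six schools, and all parents at a school share its condition and circumstances. Some of those circumstances can alter change over the six months as well as level. Under *Dietary intervention*, for example, the place of the buffet, the way food is distributed and whether lunch is served on Wednesdays differ between intervention schools. Variation of this kind passes into the difference between conditions, but the test does not count it as error.

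Enlarging the sample within schools, which is the article's only response to clustering, does not help this test: at a fixed ICC the distortion grows with the number of parents per school.

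These tests are the only inferential analysis of the second research question. There is one questionnaire and no baseline measurement of these items. A significant item could be reported as compensation, or as its opposite, when it reflects nothing more than six schools differing from one another. The same test is applied to each of the eight items.

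**Working it through.** **The plan's own figure.** The only sample size in the article is 134 children, for vegetable consumption of 13.4% against a population value of 6.7% (two-sided 5%, power 0.8). A one-sample formula reproduces it:

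n = p0·q0·[1.96 + 0.842·√(p1·q1/(p0·q0))]² / (p1 − p0)², with p0·q0 = 0.067 × 0.933 = 0.0625 and p1·q1 = 0.134 × 0.866 = 0.1160, gives 134.4.

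That number belongs to the children's lunch outcome and has no bearing on the parent comparison, for which no sample size, power, ICC or expected response is stated.

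**Inputs for the parent test.** From the article: three schools per condition, three ordered answers plus a don't-know option, and a pooled test by condition. Assumed: m responding parents per school (equal in all schools), the ICC, answer shares of 15%, 65% and 20%, and don't-know replies left out, so that each test is a 2×3 table with 2 degrees of freedom.

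**Approximation.** Design effect: DEFF = 1 + (m − 1) × ICC. The true error of a nominal 5% test on 2 degrees of freedom is about P(χ²₂ > 5.99/DEFF). For m = 60 and ICC 0.02, DEFF = 1 + 59 × 0.02 = 2.18 and the error is P(χ²₂ > 2.75) = 25.3%. Collapsed to one degree of freedom, it is 2 × [1 − Φ(1.96/√2.18)] = 18.4%.

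**Simulation.** 20,000 runs per cell, no intervention effect, Dirichlet-multinomial variation between schools. Rejection rate of the pooled 2×3 chi-square at nominal 5%:

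| Parents per school | ICC 0 | ICC 0.01 | ICC 0.02 | ICC 0.05 |
|---|---|---|---|---|
| 20 | 5.0% | 8.4% | 11.3% | 21.6% |
| 40 | 4.8% | 11.6% | 18.7% | 36.5% |
| 60 | 4.8% | 15.2% | 25.2% | 47.1% |
| 80 | 4.8% | 18.0% | 31.9% | 55.4% |

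The simulated 25.2% for m = 60 and ICC 0.02 agrees with the approximation. In terms of information, at m = 40 and ICC 0.05 the DEFF is 2.95, so 120 parents per condition count as 120/2.95 = about 41.

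A t-test on the six school proportions (4 degrees of freedom, critical value 2.78) rejected in 4.4% to 5.3% of runs over the same settings. The version with SEP level added (3 degrees of freedom) was not simulated.

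**SEP mix.** A separate simulation without clustering assumed that 30% in lower-SEP and 15% in high-SEP schools answer that the child eats more, in both conditions, with 120 respondents per condition.

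- Equal SEP shares of respondents: no bias, and rejection of 4.7% to 4.8%.
- High-SEP respondents 50 of 120 against 30 of 120: (70 × 0.30 + 50 × 0.15)/120 = 23.75% against (90 × 0.30 + 30 × 0.15)/120 = 26.25%, a spurious difference of −2.5 points; rejection 6.9%.
- 60 against 30: −3.8 points, 10.0%.
- 70 against 30: −5.0 points, 14.7%.

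Stratifying by SEP level returned rejection to about 5% in each case.

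**What six schools allow.** The smallest two-sided permutation p-value is 2/C(6,3) = 2/20 = 0.10 if the matching is ignored. If conditions are permuted within SEP level it is 2/[C(4,2) × C(2,1)] = 2/12 = 0.167. The latter reads the matching as two lower-SEP and one high-SEP school in each condition. Neither reaches 0.05.

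**The case against.** The strongest reply concerns size. With no ICC and no number of parents in the article, the inflation is assumed, and it disappears at ICC 0. The items also ask about perceived change over six months, and stable differences between schools affect change less directly than level, so the ICC may be low. This stands as a caution about magnitude. It does not rescue the test: even 20 parents per school with an ICC of 0.01 gives 8.4%, and nothing in the article argues for independence.

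A reader might go further and infer that SEP confounding is built into the comparison. The documents do not support that. Matching the schools on SEP works against such confounding, and leaving SEP out of the test biases it only if respondents' SEP mix differs between conditions, through unequal response, unequal school size or loose matching. The article gives no figures on any of these. Nor can the *Background* section be used to tie SEP to these outcomes: it links SEP to the level of diet, not to perceived change.

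A reader might also attribute the lack of randomisation to the choice of test. It is a disclosed feature of the design, and no analysis of these data removes it. Finally, the *Discussion* calls compensation a secondary objective and lists the small number of schools as a limitation. That lowers the weight of the point, but a limitation about numbers does not correct a test that overstates its evidence.

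**Conclusion.** The point holds for clustering. As fixed in the article, each of the eight tests has a type I error above 5% whenever parents' answers correlate within school, and no other part of the article corrects this. Under the assumptions of 20 to 80 equally responding parents per school, ICC 0.01 to 0.05 and three answer categories, the error lies between about 8% and 55%. The true value cannot be derived from the document.

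SEP imbalance is a conditional, secondary concern: possible if respondents' SEP mix differs between conditions, absent if it does not. The severity is should-fix, because the primary outcome is children's lunch intake and is not affected.

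**What to change.** Replace the sentence on chi-square tests with wording such as: *For each item, the proportion of parents giving each answer is calculated per school. The six school proportions are compared between conditions, giving a difference and a 95% confidence interval on the t distribution with 4 degrees of freedom, or 3 if SEP level (lower, high) is included to reflect the matching. Results are shown for each school. Any parent-level model with a school effect is supportive only and uses a small-sample correction. Six non-randomised schools support estimation and exploratory comparison, not confirmatory testing at 5%.*

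The choice between 4 and 3 degrees of freedom should be fixed in advance of the comparison. With equally weighted schools and the same SEP make-up in each condition, adding SEP leaves the estimated difference unchanged and raises the critical value from 2.78 to 3.18; it helps only if SEP explains enough of the variation between schools. The handling of don't-know replies should be stated too.

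The change affects analysis wording and code only. It needs no new data, provided each reply can be attributed to its school, which assignment to condition should already require. *Study status* says collection is complete and analysis under way, so the change should be reported openly as one made after data collection. The price is wider intervals and fewer significant results.
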